#### Walking, running and Frame Running tests

Three capacity time tests (10-m walk/run, Timed Up and Go, and 30-m Frame Running) will be conducted under standardized and comparable conditions. For children who normally use walking devices or orthoses, the child and parent will select the preferred device together and decide whether orthoses should be worn during testing. All tests will be performed with a stopwatch using the same protocol: three trials will be completed, and if the third trial is the fastest and the child is able to continue, a fourth trial will be added (maximum four trials). All trials will be video recorded to enable subsequent evaluation of gait characteristics such as number of steps, stride pattern, and movement quality. In addition, test conditions—such as the environment, motivational cues, and any unexpected events will be documented to ensure reproducibility across all assessment occasions.

*Time up and go* (TUG) is an observational assessment. TUG measures the time (in seconds) required for an individual to stand up from a standard chair, walk 3 m, turn around, walk back to the chair, and sit down again. In this study, children will start from a height-adjusted stool that allowed sitting position of approximately 90° at the hip and knees. A tape mark on the floor indicates the 3-meter turning point. The test has been widely used in clinical practice as an outcome measure to evaluate functional mobility and dynamic balance [53].

*Time test 10-meter walk/run*, means that the child walks or runs 10 m at their fastest speed.

*Time test 30 m Frame Running* means that the child completes a 30 m straight-line time trial at maximal speed using an individually fitted FR.

### Three-dimensional gait analysis

A three-dimensional twelve-camera motion analysis system (3DGA) (Vicon-UK^*Ⓡ*^, Oxford, UK) including synchronized video recordings with two digital cameras and two force plates (Kistler^*Ⓡ*^, Winterthur, Switzerland) embedded in the floor at the Motion analysis Laboratory at Astrid Lindgrens Children’s Hospital, Stockholm, Sweden is used to describe gait. With the system objective information such as pelvis, hip, knee and ankle - angles (kinematics) and forces (kinetics), and spatiotemporal parameters including step length and walking speed throughout the gait cycle are provided [54]. Ground reaction forces on the joints (kinetics) are measured from two force plates (Kistler^*Ⓡ*^, Winterthur, Switzerland) embedded in the floor. A lower limb 16 markers (10 mm in diameters) biomechanical model (plug-In-Gait). A two-dimensional video vector system can be applied giving information on direction of the ground reaction forces on the joints in case of no acceptance by the child for markers to be put on the skin. 3DGA is frequently used to describe gait, and to evaluate the effect of interventions on gait of children with CP [55, 56]. Prior to recordings, anthropometric measurements such as height, weight, and the width of the body segments will be collected before markers are placed on anatomical landmarks on the child’s body. During testing children will walk (i) barefoot, and (ii) with orthoses and/or habitual shoes on a 8 m walkway at a self-selected walking speed until three trials are obtained.

*Passive range of motion*: A physical examination including bilateral measurements of passive range of motion (pROM) of hip (flexion, extension, abduction), knee (flexion, extension, hamstrings angle), and ankle (dorsiflexion with flexed and extended knee) with a goniometer will be performed [57].

*The Modified Ashworth Scale* will be used to assess spasticity of muscles around hip, knee, and ankle. This is an ordinal scale (0, 1,+ 1 2, 3, 4) measuring resistance to passive elongation of a muscle at rest [58]. Furthermore, throughout the testing dyskinesia will be assessed as present or not (yes/no), and if present assessed as dystonia and/or chorea-athetosis (yes/no) [59]. Additionally, presence of ataxia will be observed and registered as present or not (yes/no). All examinations will be performed by experienced pediatric physiotherapists (CL, AE).

### Skeletal muscle and subcutaneous fat thickness

Objective assessment of muscle morphology will be performed using non-invasive, pain-free ultrasound imaging on three occasions over the five-month intervention period. B-mode ultrasound will be utilized to quantitatively measure skeletal muscle and subcutaneous fat thickness (in millimeters) and qualitatively assess muscle architecture (shape and grey scale analysis). Specifically, muscle thickness is measured for the thigh (encompassing the vastus lateralis and vastus intermedius muscles collectively) and the calf (medial gastrocnemius muscle) in both lower extremities at predefined positions based on anatomical landmarks, as detailed in prior publications. Measurements will be performed using a stationary ultrasound system (Canon Aplio A; Canon medical systems corporation, Tochigi, Japan).

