### Hypothesis, primary and secondary objectives

The hypothesis is that mobility performance (e.g., distance, speed, or task-specific scores) will improve during the intervention phase and remain stable or continue to improve during the post-intervention follow-up period.(Fig. 1) Furthermore, we hypothesize that the heart rate–raising activities will lead to improved cardiovascular fitness and skeletal muscle development. The assessments chosen are based on these objectives.

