### Recruitment of participants

Children will be recruited through the Astrid Lindgren Children’s Hospital and in collaboration with local habilitation services in Stockholm, Sweden. Eligible participants must meet the following inclusion criteria: a diagnosis of cerebral palsy; age 2–5 years; GMFCS level II–IV; medically stable conditions; and sufficient cognitive ability to benefit from group sessions and follow simple instructions. Both parents and children must have adequate proficiency in Swedish or English as these language skills are essential for participation in data collection and group training. Additionally, families must be able to transport the Frame Runner to training sessions.

Parents of eligible children will first receive verbal information about the study from a senior therapist who is not involved in the child´s regular treatment. Written information will subsequently be provided. Families will then have the opportunity to discuss the study in detail with the investigators before giving informed consent. Families who do not wish to participate will continue to receive usual care through their habilitation services. Eligible families will be identified by clinical staff until the target sample size is reached. This constitutes a convenience sample.

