### Sample size

The group-based intervention will include six children per group, with a total of three groups planned. We aim to include at least 18 children. This sample will allow description of response patterns at the individual level as well as analyses at the group level. Repeated measurements across study phases will make it possible to examine changes over time within participants and across the cohort, thereby strengthening the robustness and generalizability of the conclusions regarding intervention effectiveness.

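### Muscle thickness is recorded in millimetres and tested before against after, with no allowance for body size, so normal growth in 2–5-year-olds can be read as a training effect

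*Protocol article*

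**What the plan says.** - **Hypothesis.** Under Hypothesis, primary and secondary objectives, the article expects that "heart rate–raising activities will lead to improved cardiovascular fitness and skeletal muscle development".
- **Measure.** Under Skeletal muscle and subcutaneous fat thickness, ultrasound will "quantitatively measure skeletal muscle and subcutaneous fat thickness (in millimeters"). Sites are fixed "at predefined positions based on anatomical landmarks, as detailed in prior publications".
- **Visits.** The same section plans "non-invasive, pain-free ultrasound imaging on three occasions over the five-month intervention period". Table 1 places the scans at B1, B3 and F1: two before training and one after.
- **Analysis.** Statistical method compares baseline with post-intervention values and gives the paired t-test and the Wilcoxon signed-rank test as possible methods. Individual graphs of level, trend and variability complement these. No scaling to body size and no growth or age term is mentioned.
- **Population and size.** Recruitment of participants lists "a diagnosis of cerebral palsy; age 2–5 years; GMFCS level II–IV; medically stable conditions". Sample size states "We aim to include at least 18 children". The Discussion says that there is no control group.
- **Body-size data.** Under Three-dimensional gait analysis, "anthropometric measurements such as height, weight, and the width of the body segments will be collected". Table 1 places gait analysis at B2 and F1.

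**The concern.** Thickness in millimetres is itself a body dimension. In a growing child it is expected to rise whether or not the child trains. A paired test of follow-up against baseline asks whether the mean change is zero, but the hypothesis asks whether training added muscle. The two questions coincide only if growth over the interval is negligible.

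There is no control group to carry the growth component, and the plan gives the anthropometry it collects no role in the muscle analysis. A significant rise could therefore be reported in support of the muscle hypothesis when growth explains some or all of it. Objective measurement does not help here: the reading can be accurate and its cause still be growth.

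**Working it through.** The article gives no growth rate, mean thickness, SD of change or power figure for ultrasound, so there is no stated number to reproduce. The calculation below only shows scale.

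**Inputs from the article.** n = 18 (the stated minimum); paired comparison; scans at B1, B3 and F1; 12-week intervention.

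**Assumed inputs.** Height growth 6–8 cm/year; height 90–100 cm; thickness proportional to height; SD of within-child change 4–10% of thickness; two-sided 5% level; F1 directly after the 12 weeks, so B3 to F1 is 12 weeks; B1 to F1 is 16–20 weeks.

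**Step 1: gain from growth alone.** Gain (%) = 100 × (cm per year × weeks / 52) / height.

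| Interval | Low end | High end |
|---|---|---|
| B3 to F1, 12 weeks | 6 × 12/52 / 100 = 1.38% | 8 × 12/52 / 90 = 2.05% |
| B1 to F1, 16–20 weeks | 6 × 16/52 / 100 = 1.85% | 8 × 20/52 / 90 = 3.42% |

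**Step 2: threshold for significance.** With 17 degrees of freedom the critical t is 2.110. The observed mean change must exceed 2.110/√18 = 0.497 SD, which is 2.0% when the SD is 4% and 5.0% when it is 10%.

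**Step 3: chance of significance with no training effect.** This uses the non-central t distribution with non-centrality (gain/SD) × √18.

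| Interval | Gain | SD of change | Non-centrality | Chance of p < 0.05 |
|---|---|---|---|---|
| B3 to F1 | 1.4% | 10% | 0.59 | 9% |
| B3 to F1 | 2.05% | 4% | 2.17 | 54% |
| B1 to F1 | 2% | 10% | 0.85 | 13% |
| B1 to F1 | 2.5% | 5% | 2.12 | 52% |
| B1 to F1 | 3% | 4% | 3.18 | 85% |

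The nominal rate is 5%.

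**Step 4: a second set of assumptions, in millimetres.** Take thickness 15–20 mm, growth in thickness 2–8% per year and SD of change 0.5–2.0 mm. Growth over 12 weeks runs from 15 × 0.02 × 12/52 = 0.07 mm to 20 × 0.08 × 12/52 = 0.37 mm. The chance of significance runs from 5% to 84%. Again the effect may be negligible or large.

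**Step 5: can the two pre-training scans correct for growth?** Subtract the B1-to-B3 slope, scaled to 12 weeks, from the B3-to-F1 change. Let k = 12 / (weeks from B1 to B3). If the error is purely per scan, the ratio of the adjusted to the raw standard error is √{[1 + (1 + k)² + k²] / 2}. The article text does not give the baseline spacing. For assumed spacings of 6, 4 and 3 weeks (k = 2, 3, 4) the ratio is 2.65, 3.61 and 4.58. Pooling over children lowers both standard errors and leaves this ratio unchanged, so the correction is too imprecise to be the main analysis.

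**The case against.** The strongest reply is that the millimetre statement gives a unit of measurement and not an analysis scale. The article speaks of comparing raw data only for accelerometry. The tests are named as possibilities, and scaling may be set out in a fuller protocol or SAP. This stands in part: that thickness will be compared unscaled is an inference. It is nevertheless the natural reading, because the article names the unit, the visits and the tests, and gives body size no part in any of them.

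A second reply is that the design already guards against growth through two pre-training scans, inspection of trend and the Discussion's admission that causal inference is limited. These temper the interpretation but do not correct the group-level test. The graphs are individual-level and complementary, two baseline scans give a very imprecise slope, and a general caveat leaves the zero-change null in place.

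A reader might infer more than the documents support:
- **That growth will be counted as a training effect, or that a significant rise is to be expected.** The ranges above start close to the nominal 5% and rest wholly on assumptions.
- **That fat thickness shares the problem.** The hypothesis concerns muscle, and a rise in fat thickness would not be read as muscle development.
- **That the millimetre unit is the root cause.** Maturation without a control group affects the whole design, as the Discussion in effect concedes.

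**Conclusion.** The point holds for muscle thickness. As written, the plan would test a null of zero change that growth alone can violate, and it leaves unused the body-size data already being collected. Under the stated assumptions, growth gives a significant result in about 9–54% of trials over B3 to F1. Measured from B1, a growth gain of 2–3% does so in about 13–85%. The documents supply none of the growth or variability inputs, so the true figure may be near the nominal level or far above it, and nothing in the plan would show which. The change should be made, but this is not a fatal flaw: the muscle measure is not the primary outcome, and the lack of a control group is openly stated.

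**What to change.** 1. Make muscle thickness relative to body size the main muscle analysis: thickness divided by height or segment length, or change in thickness with change in height as a covariate. Keep raw millimetres as supportive.
2. Record height at each ultrasound visit. Failing that, use the B2 and F1 anthropometry: height at B3 can be interpolated, but height at B1 would have to be extrapolated. Segment length is not among the measures the article names as examples, so it would need to be added if chosen.
3. Report the pooled B1-to-B3 change beside the B3-to-F1 change as a descriptive pre-training growth reference, and say that it is imprecise.
4. State that size scaling reduces confounding by growth but does not by itself attribute the change to training.

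The cost is one height reading per ultrasound visit and a few sentences of analysis text. The ratio adds a little measurement error, and the reported gain will probably be smaller.

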### Trial design

The study uses a prospective repeated-measures intervention design with assessments conducted during baseline, intervention, and post-intervention follow-up phases. There will be three baseline measurements, a 12-week intervention phase, and three post-intervention measurements (Fig. 1 and Table 1). Primary clinical outcomes are assessed during the baseline and follow-up phases, while process-related measures, see Table 1. The total study period is approximately 5–6 months.

**Table 1 Tab1:** Assessments to be collected during the training period, B=Baseline, F=Follow up

Assessments	B1	B2	B3	F1	F2	F3
GMFM-66	X	X	X	X	X	X
Funtional Mobility Scale	X	X	X	X	X	X
Time Up and Go	X	X	X	X	X	X
pROM and tonus/MAS		X		X		
Walking/running, 10 m	X	X	X	X	X	X
Frame Running 30 m	X	X	X	X	X	X
Ultra sound	X		X	X		
Gait analysis		X		X		
Pedi-cat, mobility	X	X	X	X	X	X
Prime P/SP	X		X	X		
Accelerometry	X		X	X		X
Goa Attainment Scale			X	X		X
Parent Evaluation						X

This design is informed by principles from single-subject research designs, particularly the use of repeated baseline measurements to characterize within-participant variability before the intervention. However, we do not expect children to return to baseline when the intervention is withdrawn. The planned sample size of at least 18 participants allows also for both individual-level and group-level analyses. This is an advantage when working with heterogeneous populations, such as children with CP, where variability in the magnitude and direction of response to treatment may obscure results in randomized controlled trials (RCTs) [44]. Repeated measurements across phases also allow exploration of individual response patterns and to investigate whether participant characteristics are associated with differential responses to the intervention. Although participants and therapists cannot be blinded to the intervention, outcome assessments are conducted by independent assessors with no involvement in the training phase.

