To ensure for not blinded assessors of GMFM, we have incorporated independent, blinded secondary scoring for a random subset of 20% of the video recordings. Inter-rater reliability (IRR) will be formally assessed using Cohen’s Kappa / ICC. To proactively mitigate bias, if the initial IRR coefficients fall below [e.g., 0.80], a fully blinded primary assessor will be utilized to re-score the entire dataset.

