##### Quality assurance

Project organization will be managed by the PIs (ACE and FvW) and the study coordinator (AA). Data collection will be performed by a team of investigators, all previously experienced in collecting data from the actual assessments and not involved in the training session. Regular reviews of project progress and quality checks and quality assurance of all uploaded data will take place regularly on all data uploaded to the digital platform REDCap by one of the PIs (ACE) also responsible for exporting data when there is time for analysing data.

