### Procedure for data collection

Data collection will take place during a two-hour session at the Astrid Lindgren Children´s hospital and gait analysis will take place on a separate occasion at the Motion analysis laboratory at Astrid Lindgren Children’s Hospital, Stockholm, Sweden. Additional data collection will occur during the intervention period via weekly logbooks and questionnaires regarding the children’s engagement in training, completed through REDCap. Physical activity intensity will also be measured using accelerometry and heart rate monitoring during the training sessions and at home. The complete assessment battery and timing across all study phases are summarized in Table 2. The assessment battery was selected to address the aims of the study as well as the hypothesis. The data collection will be administrated by the study coordinator (AA). The assessors have good knowledge and experience of performing the assessments in the clinic and for research. The observational assessments will be performed by an experienced pediatric physiotherapist (EH). Skeletal muscle morphology assessments (ultrasound) will be conducted by an expert in musculoskeletal imaging (MA) and a pediatric radiologist (OK). Activity monitoring and physiological measurements during the intervention (accelerometry, heart rate monitoring) will be supervised by a medical doctor (JS) and an exercise physiologist (JN). Gait analysis will be performed at the Motion analysis laboratory by a team of lab staff and clinicians (CL, AE, KA). The study coordinator (AA) will collect questionaries and support parents to formulate individually tailored goals for each child prior to the start of the intervention. Weekly home-based training diaries and engagement questionnaires will be completed in REDCap by parents throughout the intervention period (Table 1). The different assessments that will be used and at what time points data will be collected are described in Table 1.

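### Keeping assessors out of the training does not mask baseline versus follow-up, and the article does not state that ultrasound images are read masked to visit

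*Protocol article*

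**What the plan says.** The hypothesis section predicts that "the heart rate–raising activities will lead to improved cardiovascular fitness and skeletal muscle development". The muscle part of that hypothesis is measured directly by ultrasound. The section on skeletal muscle and subcutaneous fat thickness plans "non-invasive, pain-free ultrasound imaging on three occasions over the five-month intervention period", and Table 1 places the three at B1, B3 and F1. Thickness is recorded in millimetres for one thigh and one calf site in both legs, at landmark-based positions. The same section says the images will also be used to "qualitatively assess muscle architecture (shape and grey scale analysis"). It introduces the whole assessment as objective and adds: "Measurements will be performed using a stationary ultrasound system".

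On who does it, Procedure for data collection says: "Skeletal muscle morphology assessments (ultrasound) will be conducted by an expert in musculoskeletal imaging", together with a pediatric radiologist.

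On protection against assessor bias, Trial design says that "outcome assessments are conducted by independent assessors with no involvement in the training phase". Quality assurance repeats that data collectors are "not involved in the training session". The Discussion concedes that blinding is limited and offers independent assessors, where possible, as the mitigation. The only masked reading described is for GMFM: Statistical method provides "independent, blinded secondary scoring for a random subset of 20% of the video recordings", with full blinded re-scoring if agreement is low.

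**The concern.** Every child receives the same programme and there is no control group, so there is no treatment allocation to conceal. The group-level test compares baseline with follow-up within child. What a reader must not know is therefore the visit. An assessor who never attends a training session can still know that a child has come for the post-training scan.

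Ultrasound is exposed to this in two ways. Thickness is a distance whose end points a reader sets on an image, and the reading of shape and grey scale is called qualitative by the article itself. The hypothesis has a direction, and a single post-training scan carries it. A small systematic shift in reading at F1 would enter the before-after difference in full and could not be told apart from a training effect.

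**Working it through.** **Step 1. Which blind matters.** Statistical method compares baseline with follow-up outcomes by paired tests or their non-parametric equivalents. The Discussion confirms that there is no randomization and no control group. The factor under test is visit, so the relevant blind is to visit.

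**Step 2. What each stated safeguard covers.**

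| Safeguard | Section | Hides the visit? | Applies to ultrasound? |
|---|---|---|---|
| Assessors outside the training | Trial design; Quality assurance; Discussion | No | Yes |
| Blinded second scoring of 20% of videos | Statistical method; Primary outcome measure | Intended to protect against unblinded scoring | No, GMFM only |
| Landmark-based positions, named muscles, both legs | Skeletal muscle and subcutaneous fat thickness | No; limits discretion in where to measure | Yes |
| Imaging specialists | Procedure for data collection | No; limits random error | Yes |

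No safeguard stated for ultrasound conceals the visit.

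**Step 3. What the article leaves open.** It does not say whether images are measured live or from storage, whether the person who scans also reads, or whether visit labels are visible at reading.

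**Step 4. How sensitive the comparison is.** The document gives no reader error, SD or effect size for ultrasound, so there is no figure of the plan's own to reproduce and the bias cannot be estimated. The following is an illustration under assumed shifts.

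- Inputs: n = 18 (Sample size); paired t-test (Statistical method); two-sided 5% level (assumed, none is given); no true change (assumed); shift d at F1 in units of the SD of the within-child change (assumed, range shown).
- Degrees of freedom 17, critical value 2.110, noncentrality = d × √18.
- Rejection rate = probability that a noncentral t with 17 degrees of freedom exceeds 2.110 in absolute value.

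| d | Noncentrality | Rejection rate |
|---|---|---|
| 0 | 0 | 5.0% |
| 0.10 | 0.42 | 6.9% |
| 0.25 | 1.06 | 17.0% |
| 0.50 | 2.12 | 51.6% |
| 0.75 | 3.18 | 85.0% |

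A very small shift does little harm; a moderate one does a great deal. The table does not say which of these, if any, would occur here.

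**Step 5. Reading load of a masked batch.** 18 children × 3 occasions = 54 examinations. Two sites in both legs gives 4 site images per examination, so 54 × 4 = 216 site images, each with thickness and, where applicable, shape and grey scale.

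**The case against.** The strongest reply is that the article is silent rather than wrong. It is a condensed report, and image-reading procedures for an outcome other than the primary one commonly sit in a full protocol or imaging manual; the ultrasound section itself refers to prior publications for measurement detail. Two experts are named, so scanning and reading could be separate, and the reading could already be masked. This stands in part. A reader might infer that the imaging experts know the visit when they read, or that thickness is measured live at the bedside. The documents support neither as a fact; both are inferences from silence. It would also be too strong to say that ultrasound has no protection: landmarks, specialist operators and separation from the training all limit discretion.

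The silence is not the whole of the point, however. The article does state a safeguard for outcome assessment, and that safeguard does not address the contrast being tested. It also recognises the problem for GMFM and provides masked scoring there, without extending it to images, which can be stripped of visit labels once stored.

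Further objections stand. The false-positive rates would be the same for any unmasked outcome with 18 children, and they assume no true change, whereas children aged 2–5 grow over a study of about five to six months. Growth is a rival explanation that masked reading cannot remove. Masked reading also does not reach the moment of scanning, where the operator sees the child and chooses probe position, pressure and which image to keep. Finally, ultrasound is not the primary outcome, and the Discussion already disclaims strong causal inference and admits limited blinding.

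**Conclusion.** The point holds as a worthwhile, inexpensive improvement, not as a flaw that invalidates the study. Independence from training is not a blind to visit. The article specifies masked reading for GMFM videos only, and does not state that ultrasound thickness, shape and grey scale are read masked, although they are the direct measure behind the skeletal-muscle hypothesis and rest on one post-training scan.

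The size of any bias is unknown. The 17%, 52% and 85% rates rest on assumed shifts of 0.25, 0.5 and 0.75 SD, n = 18, a two-sided 5% level and no true change; they show sensitivity and do not estimate bias in this trial. The weight is modest because the outcome is not primary and the limits on blinding are acknowledged.

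**What to change.** State in the ultrasound section, and carry out, the following:

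1. Store unmeasured images (no calipers) from B1, B3 and F1.
2. After a child's F1 scan, or after the last F1 scan of the study, remove dates and visit labels and shuffle the images within child.
3. Have one of the imaging experts already named measure thickness and grade shape and grey scale masked to visit.
4. Use these masked readings in the baseline-to-F1 analysis.

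If this is already planned, a sentence saying so is enough.

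Cost: no new scans and no new staff, but offline batch reading of about 54 examinations (about 216 site images), the work of coding and shuffling the files, and slightly later results. It assumes that images can be stored without measurements, which the article does not address.

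Limits to report alongside: the change removes bias in caliper placement and grading. It does not remove bias in probe placement, pressure or image selection at acquisition, and it does not separate training from growth.
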